## APPENDIX 1 LISTINGS OF PROHIBITED AND PRECAUTIONARY THERAPIES

### General Notes:

- Guidelines for the use of drugs with established or other potentially significant drug interactions listed in the Package Inserts of the marketed ARV agents used by subjects participating in this study (Efavirenz/Sustiva®, TDF/FTC) should be followed.
- Medications listed in the Package Inserts as contra-indicated with the other marketed ARV agents used by subjects participating in this study are not permitted.
- Any immunizations deemed appropriate by the subject's physician are permitted provided that the immunization is given > 4 weeks from any HIV-1 RNA measurement.
- A subject may not be co-enrolled in a concomitant trial unless it is approved by the Medical Monitor prior to randomization.

### Prohibited Therapies

#### Drugs that should not be administered throughout the duration of the study:

|                                                                                                              |                                                                                                                      |
|--------------------------------------------------------------------------------------------------------------|----------------------------------------------------------------------------------------------------------------------|
| Anticonvulsants: Carbamazepine, Phenobarbital, Phenytoin                                                     | Use with EFV may result in decreased concentrations of anticonvulsants or EFV.                                       |
| Oral Antifungals: Itraconazole, Posaconazole, and Voriconazole                                               | Use with EFV can result in decreased concentrations of antifungals                                                   |
| Antimycobacterials: Rifampin, Rifapentine, Rifabutin                                                         | Use with BMS-955176 can result in decreased concentrations of BMS-955176                                             |
| St. John's wort                                                                                              | Use with EFV may result in loss of antiviral therapeutic effect                                                      |
| GI motility agent: Cisapride                                                                                 | Potential for serious and/or life threatening reactions such as cardiac arrhythmias                                  |
| Pimozide                                                                                                     | Potential for serious and/or life threatening reactions such as cardiac arrhythmias                                  |
| Zetia (ezetimibe)                                                                                            | Ezetimibe is a substrate of OATP1B1 (of which BMS-955176 is an inhibitor in vitro).                                  |
| HMG-CoA Reductase Inhibitors: Lovastatin, Simvastatin, Atorvastatin, Pitavastatin, Rosuvastatin, Pravastatin | HMG-CoA Reductase Inhibitors are substrates of OATP1B1/B3 (of which BMS-955176 is an inhibitor in vitro)             |
| All drugs with antiretroviral activity other than those considered study therapy                             | Any drugs with antiretroviral activity not considered study therapy may interfere with the assessments of the study. |

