### **1.1.2 Rationale to support dose selection**

Phase 1 and Phase 2a clinical trials (AI468001 and AI468002) investigating BMS-955176 utilized a spray-dried dispersion (SDD) suspension. However, this Phase 2b study will utilize a micronized crystalline (MC) tablet.

The doses of BMS-955176 of 60 mg, 120 mg, and 180 mg MC tablet are based upon modeling and simulation and formulation considerations. A population pharmacokinetic model was developed using single dose (10 mg - 120 mg SDD) and multiple dose (10 mg to 80 mg SDD) data in healthy subjects (AI468001) as well as multiple dose data in HIV-1 clade B-infected subjects (5 mg to 120 mg SDD for 10 days, AI468002). An exposure-response analysis was conducted using data from Part A of the Phase 2a clinical trial where HIV-1 clade B infected subjects received BMS-955176 monotherapy (Dose range: 5 - 120 mg) for 10 days. The exposure-response relationship was assessed via an  $E_{\max}$  model using observed BMS-955176 steady state  $C_{\min}$ . The primary endpoint was predicted maximum viral load decline from baseline.

Steady state BMS-955176  $C_{\min}$  values in HIV-infected subjects administered MC tablet with food were projected based on the following data and assumptions:

- Exposures in HIV-infected subjects are 35% less than normal healthy volunteers based on observations from studies AI468001 and AI468002
- Single dose data was projected to multiple dosing using accumulation indices from the AI468001 study
- BMS-955176 exposures from the MC tablet formulation with food were projected based on studies AI468001 and AI468034. The impact of food on the 60 mg MC tablet dose was assumed to be that observed for the 40 mg MC suspension formulation in AI468001. Exposures to BMS-955176 120 mg MC tablet with food were determined from observed data in Study AI468034 where BMS-955176  $C_{24}$  increased approximately 70% when 120 mg MC tablet was given with a high fat meal, relative to fasted conditions. Finally, exposures to

BMS-955176 180 mg MC tablet with food were assumed to be 1.5-times that of 120 mg MC tablet with food

Figure 1.1.2-1 depicts the simulated maximum viral load decline in HIV-infected subjects administered BMS-955176 MC tablet under fed conditions.

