**Table 1.1.2-1: Exposure Multiples of BMS-955176 at NOAELa**

| Species/ Study                             | NOAEL          |                                            | Multiples    |       |        |        |
|--------------------------------------------|----------------|--------------------------------------------|--------------|-------|--------|--------|
|                                            | Dose (mg/kg/d) | Exposure                                   | PK Parameter | 60 mg | 120 mg | 180 mg |
| Rat/6-month (stomach histologic changes)   |                | No NOAEL                                   | AUC          | ---   | ---    | ---    |
| Dog/9-month (stomach histologic changes)   | 1              | AUC:
64.9 $\mu\text{g}\cdot\text{h/mL}$ | AUC          | 3×    | 2×     | 1×     |
| Dog/1-month (heart rate)                   | 20             | Cmax:
17.8 $\mu\text{g/mL}$             | Cmax         | 19×   | 10×    | 5×     |
| Dog/ Cardiovascular telemetry (heart rate) | 2              | Cp:
1.93 $\mu\text{g/mL}$               | Cmax         | 2×    | 1×     | 0.5×   |
| Mouse/EFD                                  | 45             | AUC:
197 $\mu\text{g}\cdot\text{h/mL}$  | AUC          | 10×   | 6×     | 3×     |

a Exposure multiple = animal value  $\div$  human value. Projected human Cmax values are 0.94, 1.79, and 3.61  $\mu\text{g/mL}$  and steady state AUC values are 19.3, 35.8, and 69.2  $\mu\text{g}\cdot\text{h/mL}$  at 60, 120, and 180 mg in HIV-1 subjects receiving BMS-955176 MC tablets with high fat meal, respectively. High fat meal provides the highest exposure relative to other meal types or fasted state.

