#### *Nonclinical Pharmacokinetics*

The absolute oral bioavailability of BMS-955176 was low (3.89% to 26.8%) in all preclinical species (mice, rats, dogs, and monkeys). In the dog, though there was a positive food effect and no pH dependent absorption, upon repeat dosing a less than dose-proportional increase in exposure was observed. BMS-955176 distributed preferentially into the duodenum, liver, and lymph nodes with little penetration into the brain. Protein binding was 86.1% in human serum and 78% to 94% in animal sera

In human in vitro systems, the metabolism of BMS-955176 was primarily mediated via cytochrome P450 (CYP)3A4. In vivo in rats, dogs, and monkeys, BMS-955176 was the predominant drug-related component in plasma following a single oral dose of BMS-955176. BMS-955176 was eliminated principally via metabolism followed by excretion in bile with little renal excretion.

In vitro, BMS-955176 was an inhibitor of CYP2C8 (concentration at which 50% inhibition observed [IC50] = 28.5 μM), CYP3A4 (IC50 = 32 μM), and uridine diphosphate glucuronosyltransferase (UGT)1A1 (IC50 = 20 μM) enzymes. No P-gp inhibition or time-dependent inhibition of CYPs was observed. BMS-955176 was not an inducer of CYP1A2, CYP2B6, or CYP3A4. The steady state Cmax of BMS-955176 180 mg tablet in HIV-infected patients with food is projected to be approximately 5.2 μM. Thus, the potential exists for BMS-955176 to inhibit CYP2C8, CYP3A4, and/or UGT1A1 in vivo and increase exposures to co-administered drugs that are metabolized by these enzymes. Furthermore the potential exists for drug-drug interactions (DDI) if BMS-955176 is co-administered either with an inhibitor or inducer of CYP3A4 or P-gp.

BMS-955176 was a substrate of mouse P-glycoprotein (P-gp) based on higher bioavailability in P-gp knock-out mice when BMS-955176 was co-administered with elacridar, a potent inhibitor of P-gp and breast cancer resistance protein (BCRP). BMS-955176 could not be reliably assessed as a substrate for human P-gp due to nonspecific binding and low solubility. In vitro, BMS-955176 inhibited organic anion transporting polypeptide (OATP)1B1 and OATP1B3

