(IC50 5.3 and 4  $\mu$ M, respectively), but was not an inhibitor of P gp, sodium taurocholate cotransporting polypeptide (NTCP), organic anion transporter (OAT)1, OAT3, multiple drug-resistance protein (MRP)2, and bile salt export pump (BSEP). These findings suggest a potential for DDI between BMS-955176 (as the perpetrator) and substrates of OATP1B1 and OATP1B3, but not with those of P-gp, NTCP, OAT1, OAT3, MRP2, and BSEP. Furthermore, the potential exists for drug-drug interactions (DDI) if BMS-955176 is co-administered either with an inhibitor or inducer of CYP3A4 or P-gp. Preliminary data indicate that BMS-955176 does not inhibit OCT2, a transporter that is inhibited by dolutegravir (DTG), a drug with which BMS-955176 is planned to be co-administered.

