#### **1.4.4 Drug-Drug Interactions**

In AI468001, coadministration of BMS-955176 as a single dose following two doses of 100 mg RTV resulted in an approximate 48% increase in BMS-955176 AUC(INF), consistent with

inhibition of CYP3A4 and/or P-gp. Multiple-dose administration of BMS-955176 with daily 400 mg ATV and a standard meal for 14 days resulted in a modest (~25%) increase in the BMS-955176 AUC(TAU).

Study AI468005 assessed the two-way interaction between BMS-955176 40 mg (administered as an SDD suspension) and TDF at steady state in healthy subjects. Relative to administration of each drug alone, neither BMS-955176 nor TDF exposures were meaningfully impacted upon coadministration.

Study AI468041 assessed the impact of BMS-955176 80 mg (administered as an SDD suspension) on the pharmacokinetics of the components of a combined oral contraceptive containing ethinyl estradiol (EE) and norgestimate (NGM). Exposures to both EE and norelgestromin (NGMN), the active metabolite of NGM were reduced in the presence of BMS-955176. Furthermore, one subject had a serum progesterone level > 300 ng/dL while BMS-955176 and the oral contraceptive were concomitantly administered, indicative of ovulation and contraceptive failure.

Finally, in vitro data suggest that BMS-955176 may inhibit OATP1B1 and OATP1B3 and exposures to substrates of these transporters, such as HMG-CoA reductase inhibitors, may increase when co-administered with BMS-955176.

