Similar gastric changes were seen in dogs. At 20 mg/kg/day there was single-cell necrosis of the stomach glandular epithelium. At  $\geq 3$  mg/kg/day gastric changes showed chief cell depletion. At 10 mg/kg/day changes in the stomach included: mucous cell hyperplasia correlating with increased thickness macroscopically, parietal cell depletion, single-cell necrosis of glandular epithelial cells, and modest increases in serum gastrin values. Unlike the rats, no changes were observed elsewhere in the alimentary canal including the gastroesophageal junction and the duodenum. There was no evidence of macrocytosis. Measurement of Total Protein and Albumin revealed no clinically relevant changes. The stomach histologic findings were BMS-955176 dose- and duration dependent. In the 1-month studies, vomiting and fecal changes stopped soon after dosing cessation, and microscopic lesions in the stomach and/or intestines reversed completely within a 2-week treatment-free period. In the 6 month study in rats and the 9-month study in dogs, microscopic lesions in the stomach partially recovered after a 1 month treatment free period. The NOAEL was 1 mg/kg/day (AUC 64.9 mg•h/mL) in the 9-month study in dogs, and was not established in the 6-month study in rats. Investigative studies for gastric toxicity in rats and dogs indicated similar findings with both SDD and MC forms, and with no clear evidence that the gastric toxicity is a direct local effect of BMS-955176. The mechanism and clinical relevance of these gastrointestinal findings is unknown at present (see below).

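### No Appendix 1 rule covers CYP3A4 inhibitors beyond those barred on other grounds, although the protocol reports a 48% rise in BMS-955176 AUC(INF) after ritonavir; a minor safety gap, limited to 180 mg

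*Protocol*

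**What the plan says.** Section 1.4.1.2 (Nonclinical Pharmacokinetics) identifies CYP3A4 as the main route of human in vitro metabolism and warns twice of interactions, the second time in these words: "Furthermore, the potential exists for drug-drug interactions (DDI) if BMS-955176 is co-administered either with an inhibitor or inducer of CYP3A4 or P-gp". Section 1.4.4 supplies a human observation: a single BMS-955176 dose after two 100 mg ritonavir doses "resulted in an approximate 48% increase in BMS-955176 AUC(INF), consistent with" inhibition of CYP3A4, P-gp or both. It also reports a rise of about 25% in AUC(TAU) with 14 days of atazanavir plus a standard meal, and gives no mechanism.

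In Appendix 1, the only row in which another drug alters BMS-955176 exposure is the rifamycins: "Use with BMS-955176 can result in decreased concentrations of BMS-955176". The statin and ezetimibe rows concern the opposite direction, BMS-955176 acting on other drugs. Itraconazole, posaconazole and voriconazole are prohibited for an EFV reason. Ritonavir and atazanavir are prohibited as non-study antiretrovirals.

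The general notes in Appendix 1 refer to the package inserts of the marketed antiretrovirals. Exclusions 4a and 4b refer to Appendix 1, EFV, TDF and FTC. Section 3.4.2 adds no restrictions. Section 4.5.2 allows no BMS-955176 dose adjustment.

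**The concern.** The protocol names two directions of interaction and acts on one. A drug that lowers BMS-955176 exposure has a row; a drug that raises it has none, although the rise was seen in humans. A blinded site following the text may start an unlisted inhibitor during the 96 weeks without being prompted to consider BMS-955176 exposure or to call the Medical Monitor.

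What is at stake is subject safety at the top dose. Section 1.5 says of the animal data: "The stomach histologic findings were BMS-955176 dose- and duration dependent". At 180 mg the protocol itself puts the gastric margin at 1×. Section 1.4.1.3 adds that, in preliminary data on the 180 mg tablet from AI468049, GI adverse events occurred only in the fed arms, where exposure was higher. The GI plan in Section 6.7.1.3 begins once symptoms have appeared, and Section 5.9 says individual PK results are not reported to sites.

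**Working it through.** **Inputs** (AUC in µg·h/mL)
- Projected steady-state AUC with a high-fat meal at 60/120/180 mg: 19.3 / 35.8 / 69.2 (Table 1.1.2-1, footnote a).
- Nine-month dog gastric NOAEL: 64.9 (same table). Lowest dog AUC with findings in that study: 135 (Section 1.4.1.2).
- Six-month rat study: stomach findings at every dose, lowest AUC 71, no NOAEL (Section 1.4.1.2).
- Ritonavir effect: +48% (Section 1.4.4).
- Meal effect on 180 mg AUC against fasting: 1.8-, 2.1- and 2.5-fold for light, standard and high-fat meals (AI468049, Section 1.1.2).

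**1. Reproduce the stated multiples.** NOAEL ÷ human AUC: 64.9/19.3 = 3.36; 64.9/35.8 = 1.81; 64.9/69.2 = 0.94. These round to the protocol's 3×, 2× and 1×.

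**2. 180 mg without an inhibitor.** 69.2/64.9 = 1.07 times the dog NOAEL; 69.2/71 = 0.97 of the lowest rat AUC with findings.

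**3. A second basis for 180 mg.** Section 1.1.2 also says that exposures to "BMS-955176 180 mg MC tablet with food were assumed to be 1.5-times that of 120 mg MC tablet with food". Applied to AUC, this gives 1.5 × 35.8 = 53.7, or 0.83 times the NOAEL. The table's own ratio is 69.2/35.8 = 1.93, so both bases are carried forward.

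**4. Add 48%**, assuming that it carries over to the tablet at steady state.

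| Dose and basis | AUC × 1.48 | ÷ 64.9 (dog NOAEL) | ÷ 71 (rat) |
|---|---|---|---|
| 60 mg | 28.6 | 0.44 | 0.40 |
| 120 mg | 53.0 | 0.82 | 0.75 |
| 180 mg, table | 102.4 | 1.58 | 1.44 |
| 180 mg, 1.5 × 120 mg | 79.5 | 1.22 | 1.12 |

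Only 180 mg passes either threshold. At 120 mg the AUC would have to rise more than 1.81-fold to pass the dog NOAEL. The highest figure is 102.4/135 = 0.76 of the lowest dog AUC with findings. That is only partial reassurance, because the rat threshold is lower.

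**5. Range at 180 mg.** With +25% as an illustrative lower value: 69.2 × 1.25 = 86.5 (1.33 times the dog NOAEL) and 53.7 × 1.25 = 67.1 (1.03). Footnote a notes: "High fat meal provides the highest exposure relative to other meal types or fasted state". Dosing in Section 4.5.1.2 only requires a meal. Scaling by the AI468049 ratios (an assumption) gives a factor of 2.1/2.5 = 0.84 for a standard meal and 1.8/2.5 = 0.72 for a light one. Multiples of the dog NOAEL at +25% and +48%:
- Standard meal: 1.12 and 1.33 (69.2 basis); 0.87 and 1.03 (53.7 basis).
- Light meal: 0.96 and 1.14 (69.2 basis); 0.74 and 0.88 (53.7 basis).

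The full range is 0.74 to 1.58 times the dog NOAEL, and 4 of the 12 cases fall below 1.

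**The case against.** The strongest reply is that nothing here is a contradiction. Section 1.4.1.2 says an interaction is possible; it promises no restriction that Appendix 1 then omits. The two drugs with a reported rise in BMS-955176 exposure, ritonavir and atazanavir, are both prohibited, so no subject may take the drug behind the 48%. The protocol labels no permitted drug as an inhibitor. The 48% is a single-dose result from a healthy-volunteer study that did not use the tablet. The 1× margin is disclosed and accepted. Preliminary Phase 2a data over 10 to 28 days, including arms with atazanavir with or without ritonavir, showed no clinical changes matching the animal findings. Exclusions 2b and 4b act at entry, and 4b on its wording covers the precautionary drugs too. Medications are recorded, the Medical Monitor can be consulted on GI symptoms, and sites hold the Investigator Brochure, which is not at hand.

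Most of this stands, and it limits the point to a minor one. A reader might infer that BMS-955176 exposure is protected only against rifamycins. That is true of the stated reason for each row, not of the effect: the list binds every arm, and its other rows also bar ritonavir, atazanavir and the three azoles. A reader might also infer that subjects on 180 mg will reach toxic exposure. The documents do not support this: the inhibited AUC is an extrapolation, some cases stay below the dog NOAEL, and all stay below the lowest dog AUC with findings.

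What the reply does not supply is a rule for any remaining inhibitor, at entry or started on study, or for a drug listed with an EFV caution only that also inhibits CYP3A4. Recording medications and managing symptoms come after exposure has risen.

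**Conclusion.** The gap is real but narrow. The protocol recognises that inhibitors may interact with BMS-955176, reports a human example, and gives no BMS-955176-based instruction for inhibitors outside those barred on other grounds. It matters only at 180 mg: about 50 subjects, plus any moved to that dose after the futility or Continuation Dose decision, and among them only users of a permitted inhibitor, whose number the protocol does not give.

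The size rests on carrying a single-dose AUC(INF) effect over to the 180 mg tablet at steady state with food. On that assumption AUC is 102.4 or 79.5, according to the basis used, with a high-fat meal, and lower with lighter meals. The P-gp part is weaker than the CYP3A4 part: Section 1.4.1.2 bases substrate status on mouse data and says that it could not be reliably assessed for human P-gp. A reader might infer an effect on the Week 24 result; nothing in the documents supports this, and the primary endpoint and its analysis are unaffected. This is a cheap safety improvement, not the correction of an error.

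**What to change.** Add one row to the precautionary table in Appendix 1 for strong CYP3A4 inhibitors not already prohibited, stating that they may increase concentrations of BMS-955176 and that the Medical Monitor must be contacted before use. Say in the row how strong is defined, since the protocol does not define it. P-gp inhibitors may be included, with the note that this part rests on mouse data.

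Because exclusion 4b covers everything listed in Appendix 1, add a phrase there saying that this row requires contact with the Medical Monitor and does not automatically exclude. No visit, sample size or analysis changes. The cost is an occasional drug substitution or excluded candidate.

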## Precautionary Therapies

### Drugs that should be administered with caution during the study:

|                                                                    |                                                                                                                                                                                                                 |
|--------------------------------------------------------------------|-----------------------------------------------------------------------------------------------------------------------------------------------------------------------------------------------------------------|
| Hormonal Contraceptives                                            | Hormonal Contraceptives cannot be relied upon as a highly effective method of contraception.
See Protocol Section 3.3.1 , for more information on Highly Effective Methods of Contraception. |
| Antidepressants: Bupropion and Sertaline                           | Use with EFV can result in decreased concentrations of Bupropion or Sertaline                                                                                                                                   |
| Macrolides: Clarithromycin                                         | Use with EFV can result in decreased concentrations of Clarithromycin                                                                                                                                           |
| Antimalarials:
Artemether/Lumefantrine,
Atovaquone/Proguanil | Use with EFV can result in decreased concentrations of Antimalarials.                                                                                                                                           |
| Calcium Channel Blockers                                           | Use with EFV may result in decreased concentrations of CCB's.                                                                                                                                                   |
| Benzodiazepines: Triazolam and Midazolam                           | Use with EFV can result in increased concentrations of Benzodiazepines.                                                                                                                                         |
| Dexamethasone                                                      | Use with EFV may result in reduced levels of EFV.                                                                                                                                                               |
| Avanafil                                                           | Use with EFV may result in decreased levels of Avanafil                                                                                                                                                         |

